Therapeutic ultrasound (US) is widely used for imaging purposes and regarded as an adjunct to physiotherapy. In the intensity range of 0.5–2.0 W/cm^2^, therapeutic US may have the potential to induce a variety of biophysical effects in tissues.^19^ Therapeutic US experiments on stimulation of nerve conduction and regeneration,^20 21^ and discoveries of its anti-inflammatory effects^22^ all support that therapeutic US may promote recovery of nerve compression. An RCT published in BMJ showed more pronounced subjective symptoms and electroneurographic variables for therapeutic US than sham control in patients with mild to moderate CTS.^23^ However, to our best of knowledge, no study has compared the efficacy between night splint and therapeutic US in CTS treatment yet. Additionally, some studies have also reported the efficacy of US to be used as part of a multi-intervention approach, but with low grade of study design and data.^24–29^ Therefore, the role of therapeutic US in CTS treatment still needs to be further explored by high-quality study.

Therefore, the purpose of the current three-arm, prospective, randomised, multicentre trial is to examine the effectiveness of therapeutic US in treatment for CTS, that is, night splint +therapeutic US (combined) vs night splint vs therapeutic US, on clinical and functional outcomes, including Boston Carpal Tunnel Questionnaire (BCTQ) in patients diagnosed with CTS.

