### Sample size calculation

Sample size and power calculation are based on the primary outcome of BCTQ-SSS score at 6 weeks. All sample size calculations assume two-sided analysis with a power of 90% (1-β=0.90) at a significant level of α=0.05. Based on a published RCT trial (Lancet. 2018;392:1423–1433), the authors compared corticosteroid injection and night splint for CTS, and participants in the night splint group had an SD (SD) of 0.76 points for BCTQ-SSS at their 6-week follow-up, (‘6 weeks’ was the primary endpoint in this study)),^9^ an SD of 0.76-point on BCTQ-SSS score will be used. To detect a minimum clinically significant difference of 0.8-point^53^ (superiority margin) between therapeutic US+night splint and night splint groups (assuming a true difference of 1.19-point,^9 54^ a total of 48 participants in each group is required. Allowing for an up to 10% drop-out rate, we aim to enrol at least 54 participants in each group to complete the study.

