### Analysis plan

Baseline characteristics of the three treatment groups will be summarised using appropriate descriptive statistics. Both the primary and secondary analyses will be blind analyses of treatment assignments and will be performed using the intention-to-treat^55^ method, with all randomised participants retaining their original assigned group. Multiple imputation by chained equations will be used to address missing data caused by lost access and non-response if these missing data are judged to be random.

The primary comparisons for BCTQ-SSS scores will be made using linear regression. In secondary analyses, repeated measures mixed model^56^ will also be used to examine the associations between treatments and repeated outcome measures, with terms of treatment, time, trial centre and corresponding baseline values as covariates (age, gender, body mass index, etc). Bonferroni method will be used to adjust for multiplicity.^57 58^ Linear regression will be used for numerical outcomes, and logistic/ordinal regression for any categorical outcomes.

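### The plan fixes plain Bonferroni for multiplicity, which is valid, but step-down tests with the same 0.05 family-wise bound reject everything it rejects and find more moderate true differences

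*Protocol article*

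**What the plan says.** The Analysis plan of the protocol article fixes the method in one sentence: "Bonferroni method will be used to adjust for multiplicity". It comes directly after the repeated-measures mixed model for the secondary analyses. It does not say which tests form the family: arm pairs, visits, outcomes or a mixture.

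The Introduction gives the purpose as a three-way comparison, "night splint +therapeutic US (combined) vs night splint vs therapeutic US", so each outcome has three pairwise contrasts. The Abstract makes only one of them primary: combined against night splint on BCTQ-SSS at 6 weeks. The Discussion presents ultrasound alone against splint alone as the trial's novelty.

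The Sample size calculation sizes only the primary contrast, with "a power of 90% (1-β=0.90) at a significant level of α=0.05". It takes no multiplicity adjustment and arrives at this: "a total of 48 participants in each group is required".

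**The concern.** Bonferroni tests every contrast at 0.05 divided by the number of tests, whatever the other tests show. Equality hypotheses among three arms are linked: if one pair truly differs, at most one of the other two equalities can hold. Bonferroni ignores this link, and it also ignores the simpler step-down argument that holds for any family. The contrasts outside the primary comparison, ultrasound against splint among them, were not used to set the sample size. If their true differences are moderate, power is scarce there, and the plan gives some of it away while staying well below the error rate it allows itself.

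**Working it through.** **Inputs.** From the Sample size calculation: 48 evaluable per arm; "an SD of 0.76-point on BCTQ-SSS score will be used"; two-sided 0.05; "minimum clinically significant difference of 0.8-point" (used as the superiority margin); "assuming a true difference of 1.19-point" for combined against splint. The protocol gives no effect size for the other contrasts or outcomes, so those below are assumptions, shown as a range.

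**The plan's own figure.** The margin formula gives n = 2 × (1.960 + 1.282)² × 0.76² / (1.19 − 0.8)² = 79.8, that is 80 per group and not 48. That is a separate matter. Here 48 per arm is taken as the planned size.

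**Assumed family.** The three arm contrasts of one outcome at one time point, tested for equality.

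**Procedures.**
- Bonferroni: each p at 0.05/3 = 0.0167.
- Holm: ordered p values at 0.05/3, 0.05/2 and 0.05, stopping at the first failure.
- Shaffer: smallest p at 0.05/3; if rejected, both others at 0.05.

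**Error control.** If all arms are equal, a false rejection needs the smallest of three p values to fall below 0.05/3, so the error is at most 3 × 0.05/3 = 0.05. If exactly one pair is equal, there is one true null and Shaffer tests it at 0.05 at most. No other configuration contains a true null. Every Bonferroni rejection has p at or below 0.05/3, so Shaffer and Holm reject it too.

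**Power of one pair.** The standard error is 0.76 × √(2/48) = 0.155. Power is about Φ(d/0.155 − z), with z = 2.394 at 0.05/3 and 1.960 at 0.05.

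| True difference (points) | At 0.05/3 | At 0.05 |
|---|---|---|
| 0.3 | 32% | 49% |
| 0.4 | 57% | 73% |
| 0.5 | 80% | 90% |

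Once a first pair is rejected, the step-down can recover up to about 17 points for a remaining pair.

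**Simulation.** 200,000 or more trials per scenario, 48 per arm, pooled-variance t tests on 141 df. Means are improvements for splint / ultrasound / combined. The results are the chance of finding every true difference.

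| Scenario | Bonferroni | Holm | Shaffer |
|---|---|---|---|
| 0 / 0 / 0.5 SD (0.38 points) | 35% | 41% | 50% |
| 0 / 0 / 0.6 SD (0.46 points) | 55% | 62% | 71% |
| 0 / 0.4 / 0.8 points | 24% | 47% | 48% |
| 0 / 0.3 / 1.19 points | 32% | 49% | 49% |
| 0 / 0.4 / 1.19 points | 56% | 72% | 72% |
| 0 / 0 / 0.8 points | 99.4% | 99.6% | 99.8% |
| 0 / 0 / 1.19 points | 100% | 100% | 100% |

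In the first two rows ultrasound against splint is a true null, so they say nothing about power for that contrast. Rows three to five do. In the 0 / 0.3 / 1.19 row the other two contrasts are found almost always, so the whole gain, 32% to 49%, falls on ultrasound against splint.

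**Realised family-wise error.** All arms equal: 0.044 for Bonferroni, Holm and Shaffer (0.121 unadjusted). One pair equal: about 0.017 for Bonferroni and 0.042 to 0.050 for Shaffer.

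**The case against.** Bonferroni is valid for any family, and the article states nothing false. That stands: this is a choice that can be improved, not a mistake.

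The family is undefined. The sentence follows the mixed model, and there are four follow-up visits and many outcomes, so it may not mean three contrasts per outcome. This also stands, and the Shaffer figures are conditional on that family. Holm does not depend on the definition, but its gain can be small. With an assumed 15 outcomes × 3 contrasts (45 tests), simulated power per true contrast is about 21% with Bonferroni and 22–23% with Holm at 0.5 SD, and 37–38% against 41–42% at 0.6 SD.

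A reader might therefore infer that leaving Bonferroni would recover the whole cost of a large pooled family. It would not: Holm starts at the same 0.05/45, and the gain there is 1 to 4 points. A reader might also infer that Shaffer can simply be applied outcome by outcome. If the sentence was meant to span outcomes, that would abandon control across them: the chance of any false positive over 15 outcomes with no true effects was 0.38–0.48, against 0.035–0.05 for Bonferroni over 45 tests.

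The extra power is not free in realised error either. On a single true null the false-positive rate goes from about 0.017 to as much as 0.05. It stays within the bound the plan accepts, but it is nearly three times as large.

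Finally, the effects that show a clear gain in the first two simulated rows are about half the plan's 0.8-point threshold, and Bonferroni gives matching simultaneous intervals that step-down tests do not. Both are fair limits on how much this matters.

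**Conclusion.** The point holds as a cheap gain in efficiency. Plain Bonferroni is uniformly dominated by step-down procedures with the same 0.05 family-wise bound. If the family is three equality contrasts within one outcome and time point, the chance of finding all true differences rises by roughly 15 to 24 points for moderate effects.

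The size rests on that assumed family, on 48 evaluable per arm, and on effect sizes that the protocol does not give. The gain all but vanishes when the combined arm beats both single arms by 0.8 points or more. The primary comparison, if tested alone at 0.05 as it was sized, is unaffected.

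The three-arm shortcut does not carry over to tests against the 0.8-point margin. After showing that combined exceeds splint by more than 0.8, both other margin hypotheses may still be true: a true difference of 1.19 could split into 0.595 + 0.595. Only Holm applies there.

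**What to change.** Keep the family that the Bonferroni sentence was meant to cover, state what it is, and replace Bonferroni with Holm over that family. Where the family is the three arm contrasts of one outcome at one time point, tested for equality and not against the 0.8-point margin, use Shaffer: smallest p at 0.05/3 and, if it is rejected, the other two at 0.05.

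The change should be made before unblinding, because a switch to a less conservative procedure afterwards would not be credible. It costs one sentence and a few lines of code, with no change to participants, visits, data or the primary test. The real cost is in the intervals: step-down tests have no simple matching simultaneous confidence intervals, and an ordinary 95% interval can exclude zero beside a non-significant adjusted p value. Either label the 95% intervals as unadjusted, or show Bonferroni intervals beside the adjusted p values.

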### Quality assurance/monitoring/management

In order to standardise the procedures of staff training and learning, such as participants recruitment, outcome measures, data import, security, management and analysis, a manual of operations and procedures and a case report form will be developed as per protocol, which also include the monitoring plans to assure participant protection and data integrity, thus facilitating consistency in protocol implementation and data collection. The investigators, physicians, research assistants, outcome assessors and statisticians are different people and should be trained in good clinical practice. Trained project managers will visit each centre for monitoring to ensure data quality and compliance with the trial protocol.

All data obtained will be stored electronically and strictly in a database with secure and restricted access. Encryption will be used for data transmission, with removal for any information that can identify individuals. Data will only be deidentified for analysis at the completion of this study.

### Study duration

Recruitment of the trial will begin in the November of 2021 and 1-year follow-up for all participants is anticipated to be completed by June 2023. See table 1 for time points and recruitment progress.

## Ethics and dissemination

This study has been approved by the Ethics Committee of Shanghai Sixth People’s Hospital (lead Clinical Center, approval No. 2021-152), Ethics Committee of Shanghai East Hospital (EC.D(BG).016.03.1-2021-095), Ethics Committee of Shanghai Tenth People’s Hospital (SHSY-IEC-4.1/21-194/01) and Ethics Committee of Pudong New Area People’s Hospital (IRBY2021-006). The potential risks of this clinical trial are considered minimal and are addressed in the protocol and consent form. A written consent (online supplemental file 1) will be obtained by clinical practitioners from each participant. Data will be published in peer-reviewed journals and presented at conferences, both nationally and internationally.

10.1136/bmjopen-2021-057541.supp1Supplementary data

## Discussion

CTS is a highly prevalent compression neuropathy, which results in significant paraesthesia and numbness in the median nerve distribution, especially nocturnal symptoms causing sleep disturbance, causing great socioeconomic burden. Up till now, there is still no consensus on the optimal management, and non-operative treatment is generally accepted as the first-line intervention for mild and moderate CTS. Multiple methods have been studied and reviewed in the recent decades, however, the exact efficacy still remains controversial.

In an RCT published in BMJ for mild to moderate CTS, active therapeutic US (1 MHz, 1.0 W/cm^2^) was applied to the area over the carpal tunnel in the experimental group, and indistinguishable sham US treatment was applied in the control group.^23^ At 6 months’ follow-up, satisfactory improvement or complete remission of symptoms was observed in 74% receiving active treatment, which is significantly higher than those receiving sham treatment (20%). As for electroneurography, DML and SNCV improved significantly with active treatment while remained unchanged with sham treatment. Hand grip and finger pinch strength in physical examination also improved significantly with active treatment. All results suggested satisfying effects from therapeutic US for CTS.

Therapeutic US can also be used as part of a multi-intervention approach. Some studies have compared night splint alone to night splint combined with therapeutic US in treatment of CTS, while the effects were different, and the grades of study design and data were low. Dincer *et al*^26^ found that the improvements in the combined group were statistically significantly better (p=0.043) than those in night splint alone group in BCTQ-SSS, as well as BCTQ-FSS (p<0.001), and VAS for pain (p<0.001). Similar results were also reported by Baysal *et al,*^59^ while Jothi and Bland,^27^ Sim *et al*^28^ and Armagan *et al*^29^ found therapeutic US may add no benefit to splinting in CTS.

In this study, to the best of our knowledge, it is the first to compared the efficacy between therapeutic US (therapeutic US group) and night splint (night splint group) in CTS treatment. What’s more, the additional effects of therapeutic US (therapeutic US+night splint group) in a multi-intervention approach will be compared with night splint alone (night splint group). In clinic, therapeutic US is less invasive, less expensive, safer and more portable than other nonoperative therapy like drug injections for compression neuropathy and, if proved to be effective, could be offered to selected patients as part of non-operative therapy.

There are some ongoing clinical trials on CTS treatment recent years,^60–63^ and our prospective randomised study proposes to complement and add to this relevant and much needed scientific effort.
